## Discussion

3

This study aims to improve mental health in the young by providing a low-threshold, scalable, universal mHealth preventive intervention focusing on MHL and mental well-being. Hence, this project encounters the global peak for the onset of any mental disorder at an age of 14.5 years (Solmi et al., 2022) to prevent the development of mental disorders at an early stage (Weisz et al., 2005). MHealth interventions are particularly promising since they are potentially inexpensive, easily accessible (Paganini et al., 2018), and young people are especially familiar with how to use them (Robinson et al., 2016). To date, however, there are hardly any studies that have investigated the effectiveness and acceptance of mHealth-based preventive interventions. The aim of this study is therefore the scientific evaluation of an mHealth preventive intervention. We hypothesize, that the MHG will increase participants MHL. Further we hypothesize, that the MHG will have a positive impact on participants’ mental health. In addition, we expect a good usability and acceptance of the MHG. Assumptions will be tested in a randomised controlled study design with an intervention and a waiting list control group.

Based on previous studies on universal prevention of mental disorders (Hetrick et al., 2016; Loechner et al., 2018) we expect a rather small effect size. However, effects on knowledge of mental health may be higher (Schiller et al., 2014) and rather indirectly lead to a healthier behavior. Furthermore, in case of a negative live event that may exacerbate a mental illness, participants may be better informed about their emerging symptoms early on and search for professional support and treatment. Furthermore, general well-being may be improved due to the intervention by increased emotion regulation strategies and better stress coping skills. Thus, indirect preventive effects can be achieved. Despite the consistently lower impact of universal prevention programmes compared to selective prevention programmes, the benefits of targeting the whole population can be associated with reduced stigma and is a more comprehensive approach than focusing on a selected high-risk group. The use of digital technology, including EMA, to deliver mental health content is breaking new ground in prevention and process analysis. A more pessimistic view, however, would be that the provision of attractive information material by the MHG influences neither the knowledge nor the behavior of users. Participants who are already interested in such topics and already have prior knowledge may engage with the app's content. At the same time, it is possible that although knowledge is expanded, this does not lead to a change in behavior. In this case, the study would not show any effects.

The partially open recruitment has advantages and disadvantages. On the one hand, it enables a naturalistic sample consisting of more or less motivated users with more or less interest and previous psychological stress and knowledge. This means that realistic results can be expected. On the other hand, the power of the study depends on the room for improvement or change. If the majority of users already have a high MHL, the room for change will be small, which could lead to non-significant results. To at least partially address the problem, two recruitment methods were chosen: Recruitment in school classes and open recruitment on the Internet. A review of the descriptive data at the baseline time will show whether the samples differ. In addition, the range in which the MHL is already moving at the baseline measurement time will be examined.

Another limitation of the study is that the results are only reported on self-assessment. In addition, this is a self-help intervention where participants are asked to work through the app programmes on their own without the assistance of a therapist or coach. This comes with an increased risk of dropout but speaks to scalability and anonymity. As the young people are technologically savvy and used to acquiring digital content themselves, we evaluate this risk as moderate. Furthermore, this allows us to assess how engaging the content is as a stand-alone intervention. In this context, a further limitation is that it cannot be ruled out that participants use alternative sources to the MHG to improve their MHL. Another limitation is the short time of follow-up assessment due to financial constraints of the study. However, this is a general limitation in prevention research that requires the occurrence of negative events over time to evaluate how well participants would cope with a future stressor as a result of acquired resilience. In addition, usage of content will only be tracked for the sample but not for individual participants, since personalised data from the app usage will be kept separately from scientific evaluation data. The “time spent on the app” should be considered in future studies as a moderating variable. Despite these limitations, with this study, we make a substantial contribution to closing the research gap in e-health prevention research.

## Conclusion

4

The results of this study will provide more information about the possibilities of using mHealth-based universal prevention to enhance the mental health literacy and mental well-being in a young population. This goal is very timely, as young people, in particular, were highly burdened due to the COVID19 pandemic. Universal prevention services that are cost-effective, widely available, and easy to reach are urgently needed.

## Trial status

Recruitment started in June 2023 and will be completed by the end of August 2023. Data Collection will be completed by April 2024. Data analysis has not yet begun.

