**Method:**

In a two-armed, randomised controlled study design adolescents and young adults from 14 years old will be recruited. Following an initial baseline assessment, they will be randomised to a) the intervention group (IG, *n* = 75), which will receive a mHealth intervention (the application ‘Mental Health Guide’, co-developed by lived experience experts) or b) the waiting list control group (CG, *n* = 75). Both groups will be followed up after 3 and 6 months following post assessment. We hypothesize an increase in mental health literacy in the IG compared to the CG for post and follow-up assessment (primary outcome: Mental Health Literacy Scale). In addition, we expect an improvement in mental health and psychological well-being, improved emotion regulation, reduced psychological distress, as well as good quality ratings in usability and acceptance in the use of the ‘Mental Health Guide’ We performed multiple simulations of possible outcome scenarios, incorporating an array of factors, to generate realistic datasets and obtain accurate estimates of statistical power.

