**Trial registration:**

This trial was registered in the DRKS register (DRKS-ID: DRKS00031810) on 23 June 2023.

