### Design

2.1

The study is a randomised controlled trial aiming to promote MHL and strengthen the mental health of *N* = 150 adolescents and young adults, as well as evaluating the usability and acceptance of the MHG. Fig. 1 provides an overview over the study design. In a parallel two-arm design, participants will be randomly assigned to the intervention group (IG, *n* = 75) or the waiting list control group (CG, n = 75) after a baseline online questionnaire by a computerised random generator, based on codes only. The IG will receive access to the MHG after a baseline measurement. The CG will receive access to the MHG after a post- and 3-month follow-up assessment. The relatively long waiting time of the CG until the intervention (6 months) is necessary as a comparison for the developments of the IG, but justifiable due to the preventive nature of the intervention. To capture and compare the ratings in usability and acceptance at the CG, further assessments will be administered at 6 months after the post-measurement. Additionally, to capture daily fluctuations in mood dynamics and emotion regulation, we carry out an ecological momentary assessment (EMA), to complement the pre-post-assessment with participants' experience in real-time (Schiffman et al., 2008).

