### Procedure

2.3

School classes are informed about the study and the conditions of participation by the study staff. Interested students can provide consent directly via a QR code. Interested students under the age of 18 need to forward an information letter to their parents for the initial parental consent to the study. For participants over the age of 18 who are recruited via social media, all study information will be provided, and consent will be given online. The consent form of participants is automatically followed by the digital baseline survey. In addition, participants will be prompted for the EMA survey via smartphone twice a day (at 7 am and 9 pm) for one week as part of each assessment. After the baseline questionnaire (before the EMA survey), participants receive information whether they were randomised to either the IG or CG. As soon as the EMA survey is finished, the IG will receive access to the MHG. The IG may use the MHG at their discretion and will not be prompted to use it during the 12 weeks of use.

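### The stated end of data collection (April 2024) falls before the 6-month follow-up of participants enrolled after early August 2023

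*Protocol article*

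**What the plan says.** The Trial status section gives two dates. On enrolment: "Recruitment started in June 2023 and will be completed by the end of August 2023". On closure: "Data Collection will be completed by April 2024".

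The schedule for each participant is set out elsewhere in the article:

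- **Baseline to app access (Procedure).** The EMA runs "for one week as part of each assessment", and "As soon as the EMA survey is finished, the IG will receive access to the MHG".
- **Length of use (Procedure).** The intervention group "will not be prompted to use it during the 12 weeks of use".
- **Anchor of follow-up (Abstract, Method).** "Both groups will be followed up after 3 and 6 months following post assessment". The Design section repeats the anchor for the last wave: "further assessments will be administered at 6 months after the post-measurement".
- **Role of the last wave.** The Statistical analysis section makes the second follow-up one of four time levels in the main mixed ANOVA. The Control group section gives that arm the app only between the 3-month and 6-month follow-ups.

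**The concern.** Follow-up is counted from the post assessment, not from baseline, so the last wave comes about 9 months after enrolment. From the end of August 2023 to the end of April 2024 is 8 months at most. The two sets of statements cannot both hold for late enrollees.

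Two things would be at stake if the April date were applied as a cut-off:

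- Late enrollees would have no second follow-up, which is one of the four levels of the main model for the primary outcome.
- Late enrollees in the control group would have no app ratings after access. The 6-month wave is the only one that follows their access, and the Design section gives the capture of those ratings as the reason for that assessment.

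**Working it through.** **Inputs**

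- Recruitment ends on 31 August 2023 (Trial status). The start day in June is not given. I take 1 June, which favours the document, and 23 June as an alternative because the trial was registered "on 23 June 2023".
- Data collection ends on 30 April 2024, the most generous reading of the Trial status date.
- E, the EMA week between baseline and app access, is 7 days (Procedure). E = 0 is tried as a variant.
- Use lasts 12 weeks = 84 days (Procedure). The post assessment is taken to fall at the end of use, in both arms.
- The last wave is 6 calendar months after post (Abstract and Design).
- F, a closing EMA week at the last wave, is 0 or 7 days. Procedure attaches an EMA week to each assessment; the Secondary outcomes section places it only in the first week after baseline.

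**Formula**

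Post = enrolment + E + 84 days. Last wave = post + 6 months + F.

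**Can the April date be reproduced?** Not with follow-up counted from post. Counting 6 months from baseline gives 31 August 2023 + 6 months = 29 February 2024, which would fit, but the Abstract and Design sections both exclude that anchor.

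**Last participant, enrolled on 31 August 2023**

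| E | F | Post | 3-month follow-up | 6-month follow-up |
|---|---|---|---|---|
| 0 | 0 | 23 Nov 2023 | 23 Feb 2024 | 23 May 2024 |
| 7 | 0 | 30 Nov 2023 | 29 Feb 2024 | 30 May 2024 |
| 7 | 7 | 30 Nov 2023 | 29 Feb 2024 | complete on 6 June 2024 |

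Baseline, post and the 3-month follow-up all fit before the end of April. Only the last wave does not.

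**Cross-check.** The Design section puts the control group's wait, which ends at the 3-month follow-up, at 6 months. Baseline to last wave is then 6 + 3 = 9 months, and 31 August 2023 + 9 months = 31 May 2024. This agrees with the table.

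**Latest enrolment that fits 30 April 2024**

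- E = 7: 1 August + 91 days = 31 October 2023, and 6 months later is 30 April 2024. An enrolment on 2 August gives 1 May.
- E = 0: 8 August + 84 days = 31 October 2023, again giving 30 April 2024. An enrolment on 9 August gives 1 May.

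**Share of recruitment days that are too late**

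The window is 30 + 31 + 31 = 92 days from 1 June, or 8 + 31 + 31 = 70 days from 23 June.

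| | From 1 June | From 23 June |
|---|---|---|
| E = 0 (9 to 31 August, 23 days) | 23/92 = 25 % | 23/70 = 33 % |
| E = 7 (2 to 31 August, 30 days) | 30/92 = 33 % | 30/70 = 43 % |

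If the closing EMA week must also be complete by 30 April, the late days start on 25 July: 38/92 = 41 % or 38/70 = 54 %. Reading the end date as 1 April instead of 30 April raises even the lowest figure to 53/92 = 58 %. No variant that keeps the post anchor removes the conflict.

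**The case against.** The best defence is that Trial status is a short forecast, not a stopping rule. The Abstract, Design, Table 2 and Statistical analysis sections all commit to a 6-month wave, and nothing says that anyone will be cut off. The natural reading may be that the forecast is simply too early. This stands: the conflict of dates is certain, but loss of data is conditional on the April date being enforced.

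A reader might infer more than the article supports:

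- **A number of participants lost.** Shares of days become shares of participants only under even accrual. The article does not describe accrual, and recruitment through school classes may come in clusters. The true share could be well below or above the share of days.
- **A breach of the 20 % missing-data assumption.** The article does not say whether that rate is per wave or over all observations. Spread over four waves, 25 to 43 % missing at one wave is 25/4 = 6 % to 43/4 = 11 % of observations.
- **Late enrollees dropping out of the analysis altogether.** That follows only under complete-case handling in the ANOVA, which is not stated. The additional multi-level models for the primary outcome could keep their earlier waves.
- **Loss that differs by recruitment route.** No enrolment dates by route are given.
- **A need to take the 6-month wave out of the main model.** Correcting the date makes that unnecessary, and many participants would supply the wave even under an April cut-off.

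**Conclusion.** The point holds as an inconsistency of dates. Recruitment to the end of August 2023, follow-up 6 months after post and an end of data collection in April 2024 cannot all be true. For the last enrollee the shortfall is about 3 to 4 weeks after 30 April (23 to 30 May), or just over 5 weeks with a closing EMA week (6 June).

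With a 30 April cut-off, 25 to 33 % of recruitment days from 1 June, or 33 to 43 % from 23 June, are too late for the 6-month wave. This rests on post falling at the end of the 12 weeks of use, which the stated 6-month control-group wait supports, and on the assumed start days. The share of participants cannot be given.

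If April were enforced, late enrollees would lack one of the four ANOVA levels and would be excluded from that analysis under complete-case handling. Late control-group enrollees would also lack their app ratings after access. If April is not enforced, the only error is the date.

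**What to change.** Reconcile Trial status with the Abstract, Design and Procedure sections. Restate the end of data collection as about early to mid-June 2024: the last 6-month follow-up (23 to 30 May), its EMA week if that is kept, and a response window. All participants can then complete the wave.

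If April 2024 is fixed for other reasons, say so, and state that enrolments after early August 2023 will not contribute the 6-month wave.

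The cost is one corrected date and about six more weeks of online surveys for the latest enrollees. The design, outcomes and planned models need not change if the date is moved. The registry record was not available here; if it carries the April date, it should be corrected too.
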